**3.2 Secondary Objectives**

3.2.1 To assess and compare the toxicities and morbidities of each approach.

3.2.2 To compare overall survival rates between the two treatment arms.

3.2.3 To compare recurrence in the two groups including local (gastric or esophageal bed), regional (regional lymph nodes), and distant recurrences (supraclavicular lymph node, liver, peritoneal carcinomatosis, or lung, brain, etc.).

3.2.4 To conduct an economic analysis comparing the two treatments.

3.2.5 To compare the proportion of complete (R0), microscopic positive (R1), and grossly positive (R2) resections between treatment arms.

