**7.0 Randomization**

With the completion of investigations and staging and the receipt of the baseline data recorded on the Eligibility Visit data collection forms the patient's eligibility will be re-checked and if the patient meets the inclusion and exclusion criteria, the patient will be randomized to one of two treatment groups. Blinded and blocked randomization will be in a 1:1 allocation ratio between treatment arms with stratification by surgeon. Randomization will occur centrally (Thoracic Clinical Trials Office) to ensure concealment of the process. Once randomized, the patient will be followed until death or the end of the study (1 year) and all outcome events will be attributed to the study group to which the patient has been assigned (intent-to-treat-analysis). Follow-up after 1 year will continue as per usual standard clinical practice. No clinical trial tests will be administered.

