**7.1 Overview of Treatment Plan**

The control arm of this study will consist of induction chemotherapy (2 Cycles - Cisplatin plus continuous infusion of 5-Fluorouracil) and concurrent radiation followed by surgical resection of the esophagus. The experimental arm will consist of surgical resection followed by (if required based on final pathological staging) two cycles of chemotherapy (Epirubicin, Cisplatin and continuous infusion of 5-Fluorouracil) and concurrent extended volume radiation treatment with the last 2 cycles. Follow-up of patients with clinic visits of similar frequency to the experimental arm will be required to avoid introduction of bias in recording of time to progression.

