**8.3 Surgical Quality Assurance**

**8.3.1 Completeness of Resection:** All pathology reports from patients in the study will be reviewed. Reports must contain information about gross and microscopic contamination of surgical resection margins. Tumour measurements must be recorded at surgical resection.

**8.3.2 Curative (R0):** Resections are defined as curative (complete resection: R0) when all gross disease has been removed, and microscopic examination reveals all surgical margins free of tumour, i.e., pathological stage T1-3, N0-1, M0 resected. Resections will still be considered curative if pathologic examination reveals positive lymph nodes if the gross nodes were completely resected.

**8.3.3 Palliative (R1 and R2):** Palliative resection (incomplete resection: R1 or R2) will be considered to have taken place when gross disease has been left behind (R2), or when microscopic examination reveals surgical margins which are not free of tumour (R1). Positive margins are defined as tumour at or less than 1 mm from the proximal or distal margins.

**8.3.4 No resection:** The primary tumour could not be removed.

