**11.2 Secondary Outcomes**

**11.2.1 Survival at 5 years.** All patients will be followed every 3 months for 2 years and then every 6 months up to 5 years or until death if it occurs before 5 years. Survival will be measured from randomization.

**11.2.2 Disease Free Survival.** Recurrence rates in the two groups including local (gastric or esophageal bed), regional (regional lymph nodes), and distant recurrences (supraclavicular lymph node, liver, peritoneal carcinomatosis, or lung, brain, etc.) will be compared. Disease free survival will be measured as the time from patient entry onto study until the first malignant disease recurrence.

**11.2.3 Site of Treatment Failure.** The location of the first site of malignant disease recurrence will be recorded. Local failure occurs within the gastric or esophageal bed, or regional lymph nodes. Distant failure occurs in the supraclavicular lymph nodes, liver, peritoneal carcinomatosis, pleura, lung, bones, brain, or elsewhere not considered local.

**11.2.4 Toxicities**. Possible adverse drug or radiation events will be reported as described in the London Regional Cancer Program Patient Assessment Record (PAR).

**11.2.5 Completeness of Resection.** The number of R0, R1, R2, and unresectable patients will be compared.

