**17.2 Statistical Analysis**

Descriptive statistics were generated for all patients and stratified by treatment arm for baseline patient, tumour and treatment characteristics and stratified by treatment arm for HRQOL endpoints stratified by follow-up visit, compared using the chi-square test, Fisher’s exact test, two-sample t-test, Wilcoxon rank sum test or paired t-test (compared to baseline only) as appropriate. Univariable Cox proportional hazards regression was performed for OS and DFS for all eligible variables for all patients (Supplemental Table 1 online). Kaplan-Meier estimates were generated for OS and DFS for all patients and stratified by treatment arm compared using the stratified log-rank test stratified by clinical nodal status (N0, N1). All statistical analysis was intention-to-treat and performed using SAS version 9.4 software (SAS Institute, Cary, NC, USA) using two-sided statistical testing at the 0.05 significance level. The trial was not powered to detect differences in the secondary outcomes including survival. There was no imputing, deletion, guessing, or substitution used for missing values. There were no interim analyses. There was no blinding of patients, investigators, or data analysts to the treatment allocation.

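### Completeness of resection has no category for randomized patients who never have surgery, and objective 3.2.5 sets a resections-based proportion that can overstate the control R0 rate

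*Protocol*

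**What the plan says.** Three places in the protocol define this outcome.

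- Objective 3.2.5: "To compare the proportion of complete (R0), microscopic positive (R1), and grossly positive (R2) resections between treatment arms". The unit is the resection.
- Section 11.2.5: "The number of R0, R1, R2, and unresectable patients will be compared". This adds unresectable patients, compares numbers and names no denominator.
- Section 8.3.4 defines no resection as: "The primary tumour could not be removed".

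Two general rules also apply. Section 17.2 states "All statistical analysis was intention-to-treat", and 7.0 likewise attributes outcome events to the assigned arm. Section 17.2 also states "There was no imputing, deletion, guessing, or substitution used for missing values".

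The order of treatment differs between arms (7.1). The control arm has chemotherapy and "concurrent radiation followed by surgical resection of the esophagus". For the other arm, "The experimental arm will consist of surgical resection followed by (if required based on final pathological staging) two cycles of chemotherapy".

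**The concern.** A patient who dies, refuses surgery, stops because of toxicity or develops distant disease before the operation has no R status. That patient's tumour was also not found impossible to remove. None of the four listed categories clearly fits.

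The gap is unlikely to be balanced. Control patients may start treatment up to 4 weeks after randomization (9.0, Arm I). They then receive 50.4 Gy at 1.8 Gy per fraction (10.0), which is 50.4 / 1.8 = 28 fractions, or 28 / 5 = 5.6 weeks at five fractions a week, before surgery. Experimental patients go to surgery without that interval. If R0 is reported per resection, the control denominator is selected on an event after randomization that treatment and disease course can affect, while the experimental denominator stays close to everyone randomized. The comparison then leans towards the control arm.

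**Working it through.** **The protocol's own figures.** The protocol states no R0 rate and no rate of patients not reaching surgery, so there is no figure for this outcome to reproduce. The only input it supplies is the arm size. Section 17.1 gives n = (1.96 + 0.84)² × 2 × 25² / 15² = 43.6, rounded up to 44 per arm; 44 × 1.1 = 48.4, stated as 48. I use 48 per arm.

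**Which rule places a non-operated patient?**

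| Section | What it settles | What it leaves open |
|---|---|---|
| 3.2.5 | Proportion of resections | Patients without a resection |
| 11.2.5 | Adds unresectable patients | Denominator; patients never operated on |
| 8.3.4 | Tumour could not be removed | Death, refusal, toxicity, distant progression |
| 7.0 and 17.2 (intention-to-treat) | The arm in which a patient counts | The category in which a patient counts |
| 17.2 (missing values) | No substitution | Whether an unclassified patient may be counted as not R0 |

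The intention-to-treat statements fix the arm but not the classification. If resection status is treated as missing, the last row gives no licence to count the patient as not R0.

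**Size, by assumption.** Let N = 48 be randomized per arm, k not operated, and r the R0 share among operated patients.

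- R0 among operated = r.
- R0 among all randomized = r × (N − k) / N.
- Overstatement = r × k / N.

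With r assumed to be about 90% and counts rounded to whole patients, the control arm gives:

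| Control not operated | R0 among operated | R0 among randomized | Overstatement |
|---|---|---|---|
| 2 | 41/46 = 89.1% | 41/48 = 85.4% | 3.7 points |
| 5 | 39/43 = 90.7% | 39/48 = 81.25% | 9.4 points |
| 10 | 34/38 = 89.5% | 34/48 = 70.8% | 18.6 points |

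With r assumed anywhere from 80% to 95%, the same range of k gives 3.4 to 19.7 points.

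**Effect on the comparison (same assumed r).** With 5 control patients and 1 experimental patient not operated, the experimental arm has 42/47 = 89.4% among operated and 42/48 = 87.5% among randomized.

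- Control minus experimental, operated: 90.7 − 89.4 = +1.3 points (Fisher p = 1.00).
- Control minus experimental, randomized: 81.25 − 87.5 = −6.25 points (Fisher p = 0.58).

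The sign changes, but neither result is near significance. With 5 not operated in each arm, both arms have 39/43 and 39/48, and the difference is 0 on either denominator.

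**The case against.** A reader might infer that the protocol limits the comparison to operated and unresectable patients and that the control R0 rate is therefore inflated. The document does not support that. No section says that non-operated patients are excluded, and 11.2.5 compares numbers without a denominator. In the example above those numbers are 39 and 42 R0 patients, which already point the same way as 39/48 and 42/48. The change of sign needs the resections-based denominator, and only the wording of 3.2.5 supplies one.

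A reader might also infer a flat contradiction with intention-to-treat. That too goes further than the text: where an outcome names no denominator, the general statements in 7.0 and 17.2 can be read to supply all randomized patients, and the overstatement is then zero.

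Three further limits stand.

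- The word unresectable in 11.2.5 may cover local progression before surgery, since 8.2.1 uses it for a finding of the preoperative evaluation.
- The toxicity rules in 9.4.2 tell patients to discontinue protocol therapy but do not say that surgery is cancelled, so such patients cannot be presumed lost to classification.
- Every rate used here is assumed.

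A detailed denominator rule could also stand in an analysis plan that is not at hand. That does not fully answer the point, because 3.2.5 itself states a denominator (resections), and the category list leaves out death, refusal and distant progression before surgery.

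**Conclusion.** The point holds as a conditional risk. Sections 3.2.5, 8.3.4 and 11.2.5 leave randomized patients who never have surgery without a category, and this is not reconciled with intention-to-treat or with the bar on substitution. If the proportion of resections in 3.2.5 is followed, the control R0 rate can be overstated relative to the experimental arm.

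The size cannot be derived from the protocol. The range of roughly 4 to 19 points rests on 48 per arm, about 90% R0 among operated patients and 2 to 10 non-operated control patients. Bias between the arms further requires that non-operation be more frequent in the control arm, which the treatment order makes plausible but the document does not quantify.

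Severity is minor: the outcome is secondary, and 17.2 says the trial was not powered for secondary outcomes.

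**What to change.** In 3.2.5 and 11.2.5, define the outcome as the proportion of all randomized patients who have an R0 resection. Add a category for surgery not performed, with the reason recorded (death, refusal, toxicity, progression), and count it as not R0 in both arms. Say that this is part of the outcome definition, so that it does not conflict with the rule against substitution in 17.2. Report R0 among operated patients as a descriptive figure only.

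The cost is a short wording change and a record of whether each randomized patient had surgery and, if not, why. No treatment rule changes. The downside is a lower stated R0 rate wherever patients are not operated on, probably more so in the control arm.

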**12.0 Follow-up and Data Collection**

Every effort will be made to make the outcome assessments as objective as possible as it is not possible to blind patients to the treatment arm to which the patient had been allocated.

**12.1 Follow-up Schedule**

The follow-up visits will occur at the discretion of the treating surgical, medical, and radiation oncologists. All patients will be followed for events until 60 months or death. Routine care will include a history and physical and a chest radiograph. Quality-of-Life, toxicities and morbidity data will be completed only during the first year following randomization at baseline, and every 2 months up to 1 year.

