**9.0 CHEMOTHERAPY (OPIS orders: QUINTETT-ADJ or QUINTETT–NEOADJ)**

**Arm I: Preoperative Chemotherapy (Control Arm) QUINTETT-NEOADJ**

Treatment should begin within 4 weeks of randomization consisting of 2 chemotherapy cycles concurrent with radiation. Cisplatin 25 mg/m2 days 1, 2, 3, and 4 concurrent with 5FU 1000 mg/m2 / day for 96 hours continuous venous infusion, starting with the beginning of radiation therapy. Chemotherapy should start simultaneously with the first day of radiation treatment if possible, but in no circumstance later than day 5 of radiation treatment, and not earlier than on the first radiation treatment day.

This regimen is repeated at week 5 of radiation therapy.

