**Arm II: Postoperative Chemotherapy (Experimental Arm) QUINTETT-ADJ**

Treatment should begin between 8 to 12 weeks following surgery.

The chemotherapy treatment is as follows:

Chemotherapy alone for 2 cycles – One cycle consists of Epirubicin 50 mg/ m2 and Cisplatin 60 mg/m2 day 1, and 5-Fluorouracil (5FU) by continuous venous infusion at 200 mg/m2 for 21 days.

Chemotherapy (concurrent with radiation) immediately afterwards for 2 additional cycles – One cycle consists of Cisplatin 60 mg/m2 day 1, and 5-Fluorouracil (5FU) by continuous venous infusion at 200 mg/m2 for 21 days. Concurrent radiation is to start on the same day as cisplatin is administered if possible, but in all cases within 3 days before or after that date.

Details regarding the chemotherapeutic agents:

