**9.2.4 Administration**

Postoperative chemotherapy: 5-Fluorouracil 200 mg / m2 / day continuously for 4 cycles of 21 days each, with cisplatin and epirubicin on days 1 and 22, and cisplatin on days 43 and 64 as indicated under 9.1 above. The CIV 5FU will thus continue for a total of 12 weeks, barring dose adjustments due to toxicities.

5-FU will be administered intravenously by continuous infusion through a Percutaneous Intravenous Central Catheter (PICC), or other central line, using a standard mechanical or electrical pump.

Preoperative chemotherapy: 5-Fluorouracil 1000 mg / m2 / day continuously for 4 days (96 hours) concurrently with radiation, and together with cisplatin daily (see above). This cycle is repeated starting with the 5th week of radiation therapy.

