**Arm II: Postoperative Radiation Therapy (Experimental Arm)**

Radiation treatment will begin with chemotherapy cycle 3. Concurrent radiation is to start on the same day as cisplatin is administered if possible, but in all cases within 3 days before or after that date.

Treatment planning target volume as per Yu, et al, (26) and Yu, et al (27), with minimum modification.

Target volumes

For the present protocol in post –op patients there is no GTV unless with residual disease and it should be delineated with surgical clips. GTV-P is defined as pre-op gross tumor volume as above. CTV should include the tumor bed and the anastomosis. The CTV will be 1 cm proximal of the anastomosis, 4 cm distal and 1 cm lateral, anterior, posterior beyond the pre-op GTV-P delineated by CT scan and /or endoscopy. For distal primaries celiac nodes (around T12 L1) should be included in the treatment fields.

Planning Target Volume (PTV) will provide margin around the CTV to compensate for variability in treatment set up, breathing, or motion during treatment. A margin of 1 cm around the CTV will define the PTV.

The final PTV superior margin will include the surgical anastomotic site (labeled with radio-opaque clips) proximally with 2 cm. The inferior margin of the field will be 5 cm beyond the pre-op GTV-P location. Lateral, anterior, and posterior borders will be 2 cm beyond the borders of the tumor bed and regional lymph nodes. Peri-esophageal lymph nodes will be included. A barium swallow or radio - contrast such as Esophocat® (preferred) may be obtained at the time of simulation to confirm the post -op location of the esophagus and stomach.

Treatment Plan

3D Conformal Planning

Phase I 30.6Gy/17fx (1.8Gy/fx)

The superior margin of the PTV will include the surgical anastomotic site (labelled with radio-opaque clips) proximally with 2 cm. The inferior margin of the field will be 5 cm beyond the previous GTV-P location. Lateral, anterior, and posterior borders will be 2 cm (except vertebral body posterior will be on the bony surface) beyond the lateral borders of the tumor bed and regional lymph nodes. For the distal primaries, the celiac nodes (around T12 L1) need to be included. Peri-esophageal lymph nodes will be included. Radiation fields arrangement can be APPA or multiple.

Phase II 19.8Gy /11fx (1.8Gy/fx)

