This is the coned down field to include the pre-op GTV-P bed only. The PTV-P is 5 cm proximal and distal from pre-op GTV-P. The lateral, anterior, and posterior margins will be approximately 2 cm (except vertebral body posterior will be on the bony surface) beyond the pre-op GTV-P.

Radiation fields arrangement can be multiple to come off the cord and other critical organs.

The surgical anastomotic site should receive 30.6 Gy in 17 fractions if it is not involved with disease. It should be boosted to a maximum total dose of 50.40 Gy in 28 fractions if it is close or positive margins (together either within or outside the preop GTV-P at the discretion of the treating physician).

IMRT Planning

IMRT treatment planning is permitted. Should IMRT be the treatment planning choice, 36-38 Gy/ 28 fx is to deliver to include the anastomosis and 50.4Gy/28fx is to deliver to include the tumor bed (PTV-P) only.

Normal Tissue Volume and Tolerances.

The following organs and doses by volume are guidelines for the 3D treatment plan. All normal tissues assume treatment at 1.8 Gy/fx.

Lung V20 <30% (TL-GTV), V20 <35% (TL-PTV)

Spinal Cord 10cm < 46Gy; 20cm <40Gy

Heart 1/3< 45Gy, 2/3< 40Gy, 3/3< 35Gy

Liver 1/3<40Gy, 2/3<30Gy, 3/3< 25Gy

Kidney 1/3 < 40Gy, 2/3 < 25 Gy, 3/3 < 15 Gy

Stomach 1/3< 60Gy, 2/3 < 50 Gy, 3/3 < 45Gy

Esophagus 1/3 < 60Gy, 2/3< 55Gy, 3/3 < 50Gy

Medical physicist, [name] may be contacted for additional information regarding radiation planning techniques and resources.

Therapy Interruptions

If interruption of therapy (up to two weeks) becomes necessary, radiation therapy should be completed to the prescribed doses. Total number of fractions and elapsed days should be carefully reported. If an interruption of more than 2 weeks is necessary, resumption of treatment is at the discretion of the radiation oncology chair. The patient will be considered a major deviation, but follow-up will be continued.

Criteria for Toxicity.

Acute and late toxicity related to radiation therapy include fatigue, myelosuppression, skin erythema, subcutaneous fibrosis, esophagitis, carditis, myelitis, acute radiation pneumonitis and late pulmonary fibrosis, and esophageal stricture. Acute toxicity monitoring: Acute (<- 90 days from RT start) side effects of radiation therapy will be documented using the revised NCI Common Toxicity Criteria, version 3.0 (any more recent ones?).

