Later toxicity monitoring. Late (> 90 days since RT start or persisting beyond 90 days) post-treatment complication will be evaluated and graded according to the RTOG Late Effect Radiation Morbidity Criteria.

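### Late radiation toxicity is dated from the start of radiotherapy but collected only to 1 year after randomization, so late effects that do not lead to hospitalization are observed for less time in the postoperative arm

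*Protocol*

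**What the plan says.** Comparing toxicity is the first secondary objective in Section 3.2: "To assess and compare the toxicities and morbidities of each approach". Section 12.1 limits the collection: "toxicities and morbidity data will be completed only during the first year following randomization at baseline, and every 2 months up to 1 year". Section 7.0 likewise ends the study at 1 year and leaves later follow-up to usual practice.

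Section 10.0 runs on a different clock. Acute effects are those up to "90 days from RT start) side effects of radiation therapy will be documented" with the NCI criteria. After that, "Late (> 90 days since RT start or persisting beyond 90 days) post-treatment complication will be evaluated and graded" on the RTOG late scale. No end of late grading is given there.

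The start of RT differs by arm:

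- **Control (Section 9.0, Arm I):** "Treatment should begin within 4 weeks of randomization consisting of 2 chemotherapy cycles concurrent with radiation".
- **Postoperative (Section 9.0, Arm II):** "Treatment should begin between 8 to 12 weeks following surgery". Section 10.0 adds: "Radiation treatment will begin with chemotherapy cycle 3". Section 9.2.4 fixes the cycle days, "with cisplatin and epirubicin on days 1 and 22, and cisplatin on days 43 and 64", which puts cycle 3 on day 43.

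Some recording continues after year 1. Section 12.1 follows events to 60 months, Section 12.2 requires a Special Event form for each hospitalization and death, and Section 13.0 has suspected treatment-related events adjudicated every 6 months.

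**The concern.** One clock opens the late-toxicity period at RT start, and the other closes it at a fixed time from randomization. RT starts months later in one arm, so that arm has less time in which a late effect can be seen and graded. Section 10.0 itself names late pulmonary fibrosis and esophageal stricture among the expected radiation effects. These can be graded without an admission.

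The arm with less observation is the one that Section 2.0 hypothesizes to be superior. If late toxicity is reported as the number or proportion of patients affected, part of any apparent advantage could come from the calendar. A later analysis can shorten the control window to match, but it cannot recover grades that were never collected.

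**Working it through.** **Inputs from the protocol**

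- Toxicity collection ends on day 365 from randomization, with assessments every 2 months (12.1).
- The late period opens 90 days after RT start (10.0).
- Control RT start: day 0 to 28 (9.0, Arm I).
- Postoperative chemotherapy start: 56 to 84 days after surgery (9.0, Arm II).
- Postoperative RT start: with cycle 3, with a tolerance of 3 days either side (9.0 and 10.0).

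**Input not in the protocol:** S, the time from randomization to surgery. Assumed to be 14 to 42 days, with 0 to 56 days as a wider range.

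**The plan's own schedule first.** Cycle k starts on day 1 + 21(k − 1), which gives days 1, 22, 43 and 64. Four cycles last 4 × 21 / 7 = 12 weeks. Both agree with Section 9.2.4, so RT starts 42 days after chemotherapy starts.

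**Formula.** Late window = 365 − (RT start + 90).

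**Control**

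- RT on day 0: 365 − 90 = 275 days.
- RT on day 28: 365 − 118 = 247 days.
- Either way, 5 two-monthly assessments (months 4 to 12) fall inside the window.

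**Postoperative, RT start = S + (56 to 84) + 42**

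- S = 14, gap 56: RT on day 112, late period from day 202, window 163 days, 3 assessments.
- S = 42, gap 84: RT on day 168, late period from day 258, window 107 days, 2 assessments.
- Ratio to control: 107/275 = 0.39 to 163/247 = 0.66.
- With S from 0 to 56 days, the window is 93 to 177 days and the ratio 0.34 to 0.72.

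**Does the direction depend on S?** Take the case kindest to the postoperative arm: surgery on the day of randomization, the 8-week gap, and RT 3 days early. The window is 365 − (0 + 56 + 42 − 3 + 90) = 180 days. The shortest on-schedule control window is 247 days. The two ranges do not meet, so the direction holds for any time to surgery.

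**Acute period.** At S = 42 and gap 84 the acute window closes on day 258, before day 365. On these schedules acute toxicity is not cut off in either arm.

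**Illustration only.** Assume the same constant hazard in both arms and 20% late toxicity over 247 days. The proportion seen in w days is 1 − 0.8^(w/247). For w = 107 this is 9.2%, and for w = 163 it is 13.7%. The apparent difference would be about 6 to 11 percentage points with no true difference.

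**Check of the remedy.** With S as long as 56 days and a gap of 84 days, RT starts on day 182. Collection to 24 months (730 days) then leaves 548 days from RT start, more than 12 months.

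**The case against.** Four objections carry weight.

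- **One year from randomization is the same period for both arms and respects intention-to-treat.** This stands for a comparison of any toxicity over that year, and the main comparison should stay on that footing. Sections 3.2.1 and 11.2.4 do not name late toxicity by arm as a separate endpoint. But the plan does require late grading from RT start, and the one-year cut-off curtails that grading unequally.
- **Serious late events are still caught.** This is largely right for hospitalizations and deaths, through Sections 12.1, 12.2 and 13.0. A reader might infer that late toxicity after year 1 is lost altogether, and the documents do not support that. What is lost is mainly graded late toxicity without an admission.
- **Measuring from RT start breaks the randomized comparison.** This stands. Section 10.0 does not offer adjuvant therapy to pT1N0 and pT2N0 patients in the experimental arm, whereas control patients are irradiated before final pathology is known. An analysis from RT start compares groups selected after randomization, and treating death as a competing event does not repair that.
- **The size is assumed, and the trial cannot resolve it.** A reader might infer that the postoperative arm is observed for half as long, with a spurious gain of 6 to 11 points. The first depends on a surgery date that the protocol does not give. The second also needs an assumed 20% risk and equal constant hazards, which are doubtful when one arm has the irradiated esophagus removed and the other is irradiated after reconstruction. With 48 per arm, the 95% interval for 20% against 9% to 14% is about ±14 to 15 points, wider than the illustrated bias.

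Section 10.0 could also be read as continuing late grading without limit. Section 12.1, however, restricts toxicity data expressly to the first year, so the two sections need reconciling in any case.

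**Conclusion.** The point holds in a limited form. Under the schedule as written, graded late radiation toxicity that does not lead to hospitalization is observed for 247 to 275 days in the control arm and for at most 180 days in the postoperative arm. The direction needs no assumption beyond on-schedule treatment. The range of 107 to 163 days (ratio 0.39 to 0.66) rests on surgery 2 to 6 weeks after randomization. The effect on event proportions can only be illustrated.

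Counts or proportions of late toxicity would tend to favour the experimental arm. Patients in that arm who receive no RT are a separate reason for lower counts and should not be confused with this one. The documents do not support extending the criticism to acute toxicity, to events captured by the Special Event forms, or to the comparison of any toxicity over the first year. Toxicity is a secondary outcome for which the trial was not powered, so this is a worthwhile inexpensive improvement and no threat to the primary analysis.

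**What to change.** Amend Section 12.1 so that RTOG late grades continue to be recorded after month 12 at the 3-monthly visits in Section 11.2.1, to the same date in both arms, for example 24 months from randomization. On schedule this covers at least 12 months from RT start. At the same time reconcile Section 7.0 (study ends at 1 year), Section 11.2.1 (fixed visits to 5 years) and Section 12.1 (visits at clinicians' discretion).

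For the analysis:

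- Keep the intention-to-treat comparison of any toxicity from randomization, over the longer common period, as the main comparison.
- Report late radiation toxicity among irradiated patients, over a common time since RT start, as a supportive and non-randomized description. State that pT1N0 and pT2N0 patients in the experimental arm receive no RT.

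The cost is a few more forms per patient at visits already planned. No treatment changes. If collection cannot be extended, limiting the supportive description to the same time since RT start in both arms costs nothing, but it discards control-arm data and still misses effects of later onset.
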